## Abstract

**Background:**

Cervical spondylotic myelopathy (CSM) is the most severe type of cervical spondylosis and the most common cause of spinal cord dysfunction among adults over 55 years old. MRI plays an important role in the diagnosis and evaluation of CSM, which can directly demonstrate the correlation between disc, spinal cord, posterior structures and abnormal signal in spinal cord. Static MRI can only show the static and neutral position of spinal cord, which is not enough to understand the pathogenesis of CSM. Dynamic MRI demonstrating the extension and flexion position of spinal cord can be a better tool for the treatment of CSM, especially the surgical decision making.

**Method:**

A total of 180 CSM patients who have indications for surgery will be recruited in outpatient of Peking University Third Hospital and assigned to three groups (Group A, B and C) based on their static MRI after consent. Group A (incomplete dura compression) means the signal of cerebral spinal fluid (CSF) is still visible. Group B (complete dura compression) means no CSF signal and no shape change of spinal cord. Group C (spinal cord compression) means shape change of spinal cord. Two surgical plans will be made for each participant by one professional surgeon according to the static MRI and dynamic MRI respectively and we will randomly choose one to perform via a random number system. Follow-up will be maintained at 3, 6, and 12 months after surgery through outpatient or telephone interview, including mJOA score, 10-s G&R (grip and release) and 10-s step test, SF-36 score, radiographic examination and complications. Finally, data collection and statistical analysis will be finished by researchers who are blinded to recruitment and treatment.

**Discussion:**

This study will help us to explore the indication of dynamic MRI and the value of dynamic MRI in the treatment of CSM, especially the surgical decision making. Dynamic MRI can be a useful tool in the treatment of CSM patients.

**Trial registration:**

ChiCTR1900023014. Registered on May 7th, 2019.

## Background

Cervical spondylotic myelopathy (CSM) is the most severe type of cervical spondylosis and the most common cause of spinal cord dysfunction among adults over 55 years old [1–4]. The clinical syndrome of CSM occurs when the stenosis impinges on the spinal cord, and the severity of CSM is generally thought to be related to the amount of mechanical compression of the various spinal cord tracts [5]. The symptom of CSM ranges from mild impact on the daily life to paralysis. Decompression surgery is the most appropriate treatment after the diagnosis of CSM, which includes anterior, posterior and anterior-posterior approaches [6, 7]. The diagnosis of CSM is based on clinical symptoms, physical and radiological examination including x-ray, computed-tomography (CT) and magnetic resonance image (MRI) [5]. Compare to x-ray and CT scan, MRI can directly demonstrate the disc, spinal cord and the abnormal signal in spinal cord, which is the standard examination for CSM currently [8–10]. Typically, static MRI can only show the neutral and static condition of the spinal cord, which is not adequate for the description of CSM because the cervical motion also plays an important role in the development of CSM [1, 8–13]. Dynamic MRI (dMRI) is firstly described in 1980s, which is a modification of static MRI [14]. Dynamic MRI could show the flexional and extensional position of cervical spine, which is more similar with the natural condition of cervical spine. Some changes of spinal cord would be missed in the static MRI and can be demonstrable in dMRI [13]. Extension MRI helps to identify significant cervical canal stenosis that is partially or completely absent on neutral and flexion MRI. Flexion MRI permits better visualization of hyperintense intramedullary lesions (HILs) on T2-weighted sequence [15]. For patients with cervical canal stenosis (CCS), neck extension may increase the severity of CCS due to the changes of nucleus pulposus, annulus and ligamentum flavum hypertrophy. Cervical flexion shows a relative decrease in total CCS, but the increased stenosis at the most stenotic level is more important [15, 16].

Decompressive and reconstructive surgical techniques for the treatment of CSM may be divided into anterior, posterior, and combined surgical approaches. A systematic review comparing these approaches found similar outcomes that suggest the location of the pathoanatomy may guide the surgical decision making. The choice of which approach and surgical segment to use depends on the desired region of decompression and stabilization [5, 17]. However, how to choose appropriate surgical approach and decompression segments is still controversial [18]. Traditionally, the surgical plan for CSM patients are mainly based on the symptoms and radiographic results [10, 19]. There is growing concerns about the significant value of dMRI for the assessment of CSM. Previous study suggest that preoperative extension MRI can be of great value to determine decompression levels for CSM more accurately [8, 10, 11, 15, 19]. The priorities of dMRI compared to static MRI may modify the surgical decision making and potentially improve the surgical outcome for CSM patients. In this study, we aim to conduct a randomized clinical trial that will evaluate the clinical effectiveness of dMRI in the treatment of CSM compared to static MRI, which is the standard examination currently for CSM patients. Feasibility and validation research will be carried out in our trial to explore the indication and effectiveness of dMRI in the treatment of CSM patients, especially the surgical decision making.

## Methods

### Study design

This study is a prospective, two arm, superiority and open-label randomized controlled trial, including the feasibility research and validation research Fig. 1.

**Fig. 1 Fig1:**
[figure not shown]
Study design

#### Feasibility research

Static MRI will be performed for all patients with CSM who are going to receive surgery. There are three levels of spinal cord compression, incomplete dura compression (Group A, the signal of CSF is still visible), complete dura compression (Group B, no CSF signal and no shape change of spinal cord) and spinal cord compression (Group C, shape change of spinal cord). All participants will be assigned to three groups (A, B, C) based on their static MRI and receive dMRI after consent. The compression degree and T2 high-intensity signal (T2-HIS) on those two MRI will be collected for statistical analysis.

#### Validation research

The professional surgeon will make two surgical plans for each participant according to the static MRI and dMRI, respectively. Then we will randomly choose one via a random number system to perform. Follow-up will be maintained at 3, 6 and 12 months after surgery including modified Japanese Orthopaedic Association score (mJOA), SF-36 score, 10-s G&R and 10-s step test, frontal and lateral radiography of cervical spine and complications.

Finally, we will statistically analyze the difference between static MRI and dynamic MRI to explore the indication of dMRI for CSM patients in the feasibility research. The validation research aims to identify the clinical effectiveness of dMRI in the treatment of CSM patients, especially the surgical decision making.

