#### Surgical intervention

According to the article review by Zhu et al. [20] from our institution, the surgical intervention for CSM was still controversial. Generally, the surgical approaches for CSM can be divided into anterior and posterior approaches. Anterior procedures include discectomy and corpectomy. Posterior procedures include laminoplasty and laminectomy (Table 1). In some cases, combined approach will be necessary.

**Table 1 Tab1:** surgical options

Surgical approach	Procedures
Anterior	Discectomy and corpectomy
Posterior	Laminoplasty and Laminectomy
Combined	

The level to decompression would be largely determined by patient history, physical examination findings, X-rays, CT, and conventional MRI, and dMRI would always be interpreted with the grain of salt that the compression levels might be increased by dMRI, particularly with neck extension. Additionally, the general condition and expectation of patients will also be taken into consideration before making surgical decision.

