### Sample size calculation

The sample size is calculated with reference to previous study and based on the sample size calculation formula. The average mJOA score improvement rate of surgical treatment according to static MRI in our hospital was 60.8%. we assume that the mJOA score improvement rate12 months after surgery in group dynamic MRI is 85%. We will recruit a sample of 180 participants including three groups stratified according to the spinal cord compression of static MRI. One hundred and eighty is based on a two-sided t-test, a type I error at 0.025 and type II error at 0.1 after taking into consideration a 1:1 allocation rate and a dropout rate of 20%.

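### The planned 24.2-point difference and the all-patient comparison make no allowance for patients whose static-MRI and dMRI surgical plans are the same

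*Protocol article*

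**What the plan says.** Under Validation research, one surgeon prepares a plan from static MRI and another from dMRI for every participant. The protocol continues: "Then we will randomly choose one via a random number system to perform". The Randomization section places both plans before the 1:1 choice. Neither section says what happens when the two plans are the same.

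On how plans are formed, Surgical intervention states: "The level to decompression would be largely determined by patient history, physical examination findings, X-rays, CT, and conventional MRI". It adds that "dMRI would always be interpreted with the grain of salt that the compression levels might be increased by dMRI".

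Sample size calculation gives the control value: "The average mJOA score improvement rate of surgical treatment according to static MRI in our hospital was 60.8" per cent. For the other arm, "we assume that the mJOA score improvement rate12 months after surgery in group dynamic MRI is 85" per cent. The total is justified thus: "One hundred and eighty is based on a two-sided t-test, a type I error at 0.025 and type II error at 0.1". Allocation is equal, and a 20% loss to dropout is the only allowance mentioned.

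Statistical analysis compares the dMRI arm with the static-MRI arm by intention to treat, using a t-test for continuous outcomes. Agreement between plans is not among the outcomes that the article lists.

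**The concern.** The randomised contrast exists only in patients whose two plans differ. When the plans agree, the random choice changes nothing about the operation. Patients are also not told which MRI their plan came from, so the article describes no other route to a difference between arms. The expected treatment difference in these patients is therefore zero, yet they are counted in full in both the sample size and the test.

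Two things are at stake. First, the 24.2-point planning difference depends on how often plans agree, and the article neither gives nor discusses that rate. Second, the validation research is meant to inform surgical decision making in particular. A pooled null result would be ambiguous, because dMRI might seldom alter the plan or might alter it often without benefit. These findings would have different consequences for practice.

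**Working it through.** **Inputs from Sample size calculation.** Control mean 60.8%; dMRI mean 85%; difference 85 − 60.8 = 24.2 points; two-sided α = 0.025; power 90%; N = 180; dropout 20%; 1:1 allocation. Evaluable patients per arm: 180 × 0.8 / 2 = 72.

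**Reproducing 180.** This cannot be done from the stated inputs, because no SD is given. Solving backwards, the SD that returns 90% power at 72 per arm is about 40.8 points by the non-central t (41.2 by the normal approximation). I use 40.8 as an assumption and show smaller values.

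**Reading 1: 24.2 points is the gain where plans differ.** Let c be the share of identical plans.
- All patients: the expected difference is 24.2 × (1 − c), with 72 per arm.
- Differing plans only: the expected difference is 24.2, with 72 × (1 − c) per arm.

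Power by the non-central t, two-sided 0.025, SD 40.8, with the same SD and dropout assumed in both subsets:

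| c | All-patient difference | Power, all patients | Per arm, differing plans | Power, differing plans |
|---|---|---|---|---|
| 0% | 24.2 | 90% | 72 | 90% |
| 10% | 21.8 | 82% | 64.8 | 86% |
| 20% | 19.4 | 72% | 57.6 | 82% |
| 40% | 14.5 | 45% | 43.2 | 68% |
| 50% | 12.1 | 32% | 36 | 59% |

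Sensitivity to the SD at c = 50%: with SD 30, 56% against 87%; with SD 25, 74% against 96%. At c = 20% and SD 30, all-patient power is still about 94%. The loss therefore depends on both c and the SD.

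**Reading 2: 24.2 points is the whole-arm effect.** Power is then as planned, but the gain where plans differ must be 24.2/(1 − c): 26.9 points at c = 10%, 30.2 at 20%, 40.3 at 40% and 48.4 at 50%.

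Whether such gains are possible depends on a ceiling. Suppose the improvement rate is capped at 100%, and let m be the mean in agreeing patients. The dMRI arm can reach 85% only if c·m + (1 − c)·100 ≥ 85, that is, c·(100 − m) ≤ 15.
- m = 60.8: c ≤ 15/39.2 = 38%
- m = 70: c ≤ 50%
- m = 75: c ≤ 60%
- m = 80: c ≤ 75%
- m ≥ 85: no limit

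**What the article says about c.** It gives no figure. Surgical intervention suggests frequent agreement on levels, because the inputs that mostly set them are shared by both plans. The Discussion points the other way: in one cited study, 3 of 4 reviewers significantly increased the number of levels after seeing dMRI. A plan also covers approach and procedure, so agreement on levels alone is not full agreement.

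**The case against.** The strongest reply is that the trial asks a strategy question: is planning with dMRI better than planning with static MRI? An intention-to-treat comparison of all randomised patients answers that without bias. The 85% is stated for the dMRI group as a whole, so it may already average over agreeing and differing plans. The details of subset analyses can also be left to an analysis plan that is not shown. The first point stands, and the all-patient comparison should remain primary. The second stands as a possible reading, and it means that the power figures under Reading 1 are scenarios. It does not remove the difficulty, because the whole-arm 85% then implies a gain in differing-plan patients that grows with an undisclosed c. The third does not reach the planning difference, which is fixed in this document.

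Two stronger conclusions are tempting. A reader might infer that the 24.2-point gain becomes unattainable once about 38% of plans agree. That needs a 100% ceiling, although the mJOA section does not define the rate. It also needs a static-plan mean of 60.8% in agreeing and differing patients alike. If patients with differing plans do worse on the static plan, the limit rises or disappears. A reader might also infer that the stated 90% power is not delivered. That follows only if 24.2 points belongs to differing-plan patients and the SD is near the back-solved value. The documents establish neither.

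Finally, the differing-plan analysis does not restore 90% power at SD 40.8. It only loses less.

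**Conclusion.** The concern holds in limited form. Patients with identical plans contribute no contrast, some agreement is likely on the protocol's own description of planning, and neither the sample size nor the analysis allows for it. The strategy comparison is not biased. The weakness is that the planned effect rests on an unstated agreement rate and that a null result would be hard to interpret.

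The size is conditional. With 24.2 points as the gain where plans differ and SD 40.8, all-patient power falls from 90% to between 82% and 32% as c goes from 10% to 50%. The differing-plan comparison has 86% to 59% over the same range, and it had the higher power at every non-zero c tested. Smaller SDs shrink the loss. The actual c and SD are unknown, so none of these figures is a property of the trial as it will run.

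**What to change.** 1. Before randomisation, record both plans (approach, levels, procedure) and a same/different flag with a written definition of sameness. Both plans already precede the random choice, so the flag is a baseline characteristic and the differing-plan subset keeps its randomised comparison. If it were classified after allocation, knowledge of the allocation could influence it.
2. Keep the all-patient intention-to-treat comparison as the primary analysis of the imaging strategy.
3. Pre-specify the randomised comparison in differing-plan patients as a key supporting analysis of dMRI's effect on surgical decisions.
4. Report the agreement rate as a result.
5. In the sample size section, state the expected c and the SD, say whether 24.2 points refers to the whole arm or to differing-plan patients, and give power conditional on these.

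Stratifying randomisation by the flag is optional.

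The cost is one extra data field, one extra pre-specified analysis and probably a less favourable stated power. No extra patients are needed for these steps.

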### Recruitment and informed consent

This single-center study will be conducted in Peking University Third Hospital. Patients with CSM who need surgical treatment will be recruited from outpatient of Peking University Third Hospital. After confirming the eligibility of the patients, the researcher will discuss the study goals, procedures, activities and possible alternatives for approximately 20 min, and answer all questions. After enrolment, participants will be coded as a unique number and general information will be collected.

### Eligibility

The inclusion and exclusion criteria are as follows.

The inclusion criteria:
➢ Diagnosis of cervical spondylotic myelopathy (CSM)➢ No surgical contraindications➢ Willing to receive surgery➢ Willing to take part in our study

The exclusion criteria:
➢ Other diseases in cervical vertebra (trauma, tumor, infection)➢ Age < 18

### Randomization

Patients will be recruited from outpatient and eligible participants will be enrolled in the study after informed consent. The treating surgeon will also confirm the eligibility before making two surgical plans based on the static MRI and dMRI, respectively. A researcher will randomly choose one from the two surgical plans via a random number system. Randomization of experiment group (dMRI) and control group (static MRI) will be on a 1:1 basis.

### Blinding

As the surgical plans should be informed to patients clearly, the patients cannot be blind to their surgery. However, all patients won’t know which MRI the surgical plan is from. In addition, the treating surgeon will also not be blind to the treatment but will not take part in the preoperative and postoperative research assessment. The clinical outcome data will be collected by independent research assistants who are blind to the surgical decision making.

### Interventions

The surgical indication of Patients with CSM is mainly based on the symptoms, physical and radiographic examination. All participants will receive routine examination at admission, including blood routine and evaluation of general condition. Imaging examination as X-ray, CT and MRI will be accomplished before making surgical plan. All patients will receive imaging examination immediately after surgery and follow-up will be continued at 3, 6 and 12 months after surgery. This trial will involve two types of MRI: static MRI and dynamic MRI. These two types of MRI will be performed in the supine position.

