#### Dynamic MRI

Dynamic MRI will show the flexional and extensional position of cervical spine other than neutral position. The angle of extension and flexion is as can be tolerated and it will take longer time than static MRI. The extension and flexion are accomplished by a self-designed posture cushion (Fig. 2). All participants in this study will receive dynamic MRI after informed consent for free. The same evaluation as static MRI will be carried out for dMRI.

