### Data management

All participants will receive a study number and all data about patients will be recorded via this number. All information about participants including baseline information, radiographic outcomes, surgery and follow-up will be secured in Peking University Third Hospital. Data will be collected at baseline admission and 3, 6 and 12 months after surgery. One professional surgeon will make the surgical plan and finish the surgery in Peking University Third Hospital. The researchers will collect the baseline information and maintain the follow-up after surgery. Data entry, transfer and subsequent maintenance will be performed by a data manager. Access to study data is restricted to the study research team.

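### The static-MRI control plan is not protected from the dynamic MRI: one unblinded surgeon writes both plans, and nothing withholds the dMRI while the control plan is written

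*Protocol article*

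**What the plan says.** The protocol article fixes these elements:

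- **Who plans.** The abstract's Method paragraph: "Two surgical plans will be made for each participant by one professional surgeon according to the static MRI and dynamic MRI respectively". Data management adds: "One professional surgeon will make the surgical plan and finish the surgery".
- **Who is scanned.** Under Dynamic MRI: "All participants in this study will receive dynamic MRI after informed consent for free". Table 2 places both MRI examinations at admission.
- **When planning happens.** Under Interventions: "Imaging examination as X-ray, CT and MRI will be accomplished before making surgical plan". The same paragraph later adds: "This trial will involve two types of MRI: static MRI and dynamic MRI".
- **What is randomised.** Under Randomization: "The treating surgeon will also confirm the eligibility before making two surgical plans based on the static MRI and dMRI, respectively". Then: "A researcher will randomly choose one from the two surgical plans via a random number system".
- **Who is masked.** The Blinding section keeps the source of the plan from patients and masks the outcome assessors. It states that the treating surgeon is not blind. It says nothing about what the surgeon may see while drafting each plan.
- **How levels are chosen.** The Surgical intervention section lists history, examination, X-ray, CT and conventional MRI as the main determinants. It continues: "dMRI would always be interpreted with the grain of salt that the compression levels might be increased by dMRI". It does not say to which of the two plans this applies.

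**The concern.** The trial sets out to compare surgery planned with dMRI against surgery planned with static MRI, which the Background calls the current standard. The draw between the two finished plans is the only randomised element. The comparison of compression grade on static MRI and dMRI is made within patients. The control therefore has to be the plan a surgeon would write without the dMRI.

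The article expects dMRI to show more compression than static MRI. If the surgeon has already seen that, the static plan may take it into account, even without intent. This would happen before the draw, so randomisation cannot remove it. Intention-to-treat analysis and masked assessors cannot remove it either, and a static plan written after sight of the dMRI cannot be reconstructed later.

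At stake is the interpretation of the randomised mJOA comparison. A null result could mean that dMRI adds nothing, or that the control arm had part of its benefit. A positive result could partly reflect an unblinded planner writing two plans that differ more than independent planning would produce.

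**Working it through.** **1. Does the text set an order between the static plan and sight of the dMRI?**

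- Interventions puts imaging, including MRI, before planning. The word MRI there might mean only routine static MRI, but the same paragraph then names both types as part of the trial.
- Table 2 schedules both scans at admission, and all participants have the dMRI.
- Randomization has both plans written before the draw.
- Blinding leaves the surgeon unmasked.

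Together these allow the dMRI to be available to the surgeon before either plan is written. No section withholds it or requires the static plan to be finished first. Equally, no section says that the surgeon does look at it first.

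**2. Do the planning descriptions agree?** Randomization ties one plan to each type of MRI. Surgical intervention describes one process of level selection that mentions both types and says dMRI is always interpreted, with caution. The two descriptions agree only if the second is confined to the dMRI plan, and the text does not confine it.

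**3. How sensitive is the trial to a loss of contrast? (illustration)**

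Inputs from Sample size calculation: improvement rates of 60.8% and 85%, two-sided t-test, alpha 0.025, type II error 0.1, 1:1 allocation, 20% dropout, N = 180.

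- Difference: 85 − 60.8 = 24.2 points.
- Evaluable: 180 × 0.8 = 144, or 72 per arm.
- No SD is given, so the 180 cannot be reproduced as a t-test figure. It can only be inverted to find the SD it implies. With the normal approximation, SD = Δ × √(n/2) / (z₀.₉₈₇₅ + z₀.₉₀) = 24.2 × √36 / (2.241 + 1.282) = 145.2 / 3.523 ≈ 41.2 points.
- Standard error of the difference: 41.2 × √(2/72) ≈ 6.87 points.

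Let c be the share of the 24.2 points lost. The documents do not give c, so the values below are assumptions. Power ≈ Φ(24.2 × (1 − c) / 6.87 − 2.241).

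| c (assumed) | Remaining difference | Difference / SE | Power |
|---|---|---|---|
| 0% | 24.2 | 3.52 | 90% |
| 10% | 21.8 | 3.17 | 82% |
| 25% | 18.2 | 2.64 | 66% |
| 40% | 14.5 | 2.11 | 45% |

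The 90% in the first row holds by construction, because the SD was chosen to give it. Using the exact t distribution with an SD of 40.8 (the value that gives 90% power under that distribution) yields 82%, 66% and 45% for the lower rows, so the choice of method is immaterial.

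**The case against.** The strongest reply is that this rests largely on silence in a condensed article. Three sections tie the two plans to separate image sources, and the order of image release is the kind of detail a full protocol or manual may hold. Performing a scan is also not the same as showing it to the planner. The Interventions sentence follows one about routine admission examinations, so its MRI may mean static MRI only. The Surgical intervention sentence can be read as a caution about the dMRI plan alone.

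Much of this stands, and it rules out three stronger readings that a reader might infer:

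- *That the control plan is contaminated.* The documents do not show this. They set no order between the static plan and sight of the dMRI, so contamination is possible but not established.
- *That the bias must run toward no difference.* Dilution is the likely form, but a surgeon who knows both sources and writes both plans could also drive them apart.
- *That a planned endpoint on the proportion of plans changed by dMRI is biased.* No such outcome appears among the primary or secondary outcomes.

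The design also has merits. One surgeon writing both plans removes between-surgeon variation, and completing both plans before the draw means that allocation cannot shape them.

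What does not stand is that this is only omitted detail. The article describes planning, randomisation and blinding explicitly, and those descriptions leave the comparator unprotected. What the planner may see defines the control intervention. The tension between Randomization and Surgical intervention lies in the stated text and not in a gap.

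**Conclusion.** The concern holds in conditional form. As written, the plan lets the static-MRI plan be influenced by the dMRI, so the control arm may not represent planning without dMRI. Because this would enter before randomisation, no later safeguard in the article corrects it.

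Its size in this trial is unknown. The figures of about 82%, 66% and 45% power are a sensitivity range. They rest on an SD of about 41 points inferred from N = 180 and on assumed losses of 10%, 25% and 40%. They describe dilution only and say nothing about exaggeration of the difference. They do show that even a modest loss of contrast would use up a material part of the planned power.

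**What to change.** State the sequence in the protocol:

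1. The surgeon writes, time-stamps and locks the static-MRI plan with the dMRI images and report withheld.
2. The dMRI is then released and the dMRI plan is written and locked.
3. Randomisation follows.

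Reconcile the level-selection paragraph in Surgical intervention with the two-plan description in Randomization, so that it is clear which information feeds which plan. Record any departure of the operation performed from the allocated plan, because the operating surgeon will by then know both.

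The cost is a procedural sentence and a locked form, with the same surgeon, scans and patients and no extra staff. The downside is a small scheduling constraint on image release. The rule has to be in place before a participant's plans are written, because it cannot be applied afterwards.
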